### Research governance

The study is funded by the UK National Institute for Health Research Health Technology Assessment programme, and is sponsored by the University of Birmingham. Ethical approval was obtained in July 2014 from Edgbaston NHS Research Ethics Committee, West Midlands, UK (14/WM/1036). The study is overseen by an externally appointed Study Steering Committee comprising three subject experts (two Public Health specialists with an interest in childhood obesity prevention and management, and an expert on equality and diversity in relation to health and care) and a public representative.

All data are stored securely and confidentially in accordance with University of Birmingham data protection policies. Feasibility study data are entered into a secure database, developed and maintained by the Birmingham Primary Care Clinical Research and Trials Unit.

## Discussion

This study attempts to address the important issue of the provision of children’s weight management services that are relevant to all ethnic and cultural communities within the UK. There is little existing research on culturally adapted children’s weight management interventions [14–16], and none based in the UK. Whilst the focus of the phase 1 intervention adaptation is to ensure the children’s weight management programme is more suitable and engaging for Pakistani and Bangladeshi families, the overall aim is to ensure the developed programme is adaptable to the needs of families from all communities. If programme adaptation successfully increases the likelihood of programme completion by families, then this programme has the potential to be rolled out across the UK after evaluation to assess programme effectiveness.

The intervention adaptation process uses two theoretical frameworks, each fulfilling a specific purpose. The BCW [28] guides the theoretical development of a complex intervention, enhancing the capabilities, opportunities and motivation to change target behaviours within families attending the programme. The typology of cultural adaptation and health promotion programme theory [21] enables us to explicitly identify the adaptations required to ensure cultural barriers are minimised, and develop a programme that better meets the cultural needs of a wider audience.

A need for direct comparisons between existing health promotion programmes and those that are adapted for minority ethnic groups has been highlighted [21]. Phase 2 of this study directly compares the adapted programme to the standard programme, and evaluates the success of programme adaptation through several methodologies. The feasibility study also enables further refinement of the adapted programme and allows us to gather information to inform a trial evaluating programme effectiveness. This study will provide important information on both the feasibility of recruitment in a culturally and ethnically diverse population, and likely attrition rates in a trial. The process of home visits for data collection is a particular strength of the study design as it is likely to minimise attrition. A range of outcome measures that relate to the intervention are being tested in the feasibility study. This will enable identification of the primary outcome measure and important secondary outcome measures for inclusion in a future trial to evaluate programme effectiveness. We recognise that multiple outcome measures may overburden participants, and the feasibility study gives us the opportunity to assess this and prioritise which outcome measures to include in a future trial. The feasibility study also provides the opportunity to develop rigorous methodology for process and cost-effectiveness evaluation for use in a future trial. These are key areas to address in the definitive evaluation of complex interventions [27, 28].

The decision to undertake a full scale trial to evaluate clinical and cost-effectiveness of the adapted programme will primarily depend on the success of the programme at increasing family completion rates, and the acceptability of the programme to families from all cultural backgrounds. If we progress to a full trial, the valuable information gained on the feasibility of study design, processes and data collection will shape trial design and inform a sample size calculation.

### Study status

The study is registered on the International Standard Randomised Controlled Trial Register (ISRCTN81798055). Phase 1 was undertaken between September 2014 and August 2015. Participant recruitment for the phase 2 feasibility study commenced in September 2015 and is due to finish in April 2016, and final follow-up measures will be undertaken by October 2016.

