## Methods/design

### Study design

The first phase addresses the theoretical and modelling stages of the UK Medical Research Council (MRC) framework for the development and evaluation of complex health interventions [27, 28] and involves adaptation of the current children’s weight management programme delivered in Birmingham. The adaptation process will be informed by evidence for effective childhood weight management intervention, and the experiences and perceptions of Pakistani and Bangladeshi families who have participated in or declined to participate in the current programme. The second phase is a two arm cluster-randomised feasibility study that compares the adapted programme to the existing programme, addressing the feasibility stage of the MRC complex health intervention framework. Data will be collected from participants at three time points: before programme attendance, after programme completion and 6 months after programme completion. A summary of the study design is shown in Fig. 1.

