### Setting

The proposed study takes place in the UK’s second largest city (Birmingham) with a population of nearly 1.1 million; 16.5 % from Pakistani and Bangladeshi communities. Children from these communities comprise 26 % of the Birmingham population aged 0–15 years [23].

First Steps, the children’s weight management programme to be adapted, is commissioned by Birmingham City Council and delivered by Birmingham Community Healthcare NHS Trust. All families in Birmingham with a child of primary school age (4–11 years) who has a BMI over the 91st centile of the UK 1990 growth reference charts [29] are eligible to attend First Steps. Referral pathways to the programme include through health professionals, schools, the National Child Measurement Programme (NCMP; a BMI measurement programme for all school children aged 4–5 years and 10–11 years), and self-referral. First Steps is a group-based programme delivered as seven one-hour sessions over 6–7 weeks in community venues. Session content covers nutrition education, behaviour change and physical activity promotion. Parents/carers attend all sessions and children accompany them for the first and last sessions, when children’s heights and weights are measured. Participants for both phases of the study will be identified through the current children’s weight management services. The existing service infrastructure will be used to deliver the intervention and comparator programmes in the phase 2 feasibility study.

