### Participants

Families in Birmingham with a child age 4–11 years who is overweight (defined as greater than 91st centile for BMI on the UK 1990 growth reference charts [29]) and who are referred to the existing children’s weight management service within the study recruitment period will be eligible to participate. Local service data indicate that 40 % of referrals are Pakistani and Bangladeshi families; however, as the intervention will be adapted primarily to suit Pakistani and Bangladeshi families, we aim to recruit 60 % of participants from these communities and therefore will prioritise recruitment of these families. This will enable us to explore the success of programme adaptation from the perspective of these families. Approximately 800 children and families of all ethnicities are referred to the First Steps programme annually. We aim to recruit 80 children and their families in a 6-month period, and therefore need to recruit 20 % of referred families to participate in the study.

Families referred to the weight management service will initially receive a study invitation letter and information leaflet from the service providers, which will be followed up by a telephone call. If they are interested in participating in the study, they will be contacted by a researcher to arrange a time for an initial home visit to gain consent and collect baseline data. Home visits are anticipated to maximise participation and assist in timely data collection. This data collection process will also allow for blinding of researchers undertaking data collection in a future trial. If a parent/carer requires communication in another language, a person who speaks the relevant language will contact them by telephone to explain the study and invite them to participate, and will complete the initial visit. Written consent will be gained from participating parents/carers, and assent will be gained from children (written if 8 years or more and verbal if under 8 years).

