### Outcome data collection procedure

Physical measurements and other assessments will be undertaken on children and parents/carers at three time points: baseline, post-intervention and 6 months post-intervention. Trained research staff will undertake data collection in the participant’s home, or at another location convenient to the participant’s family. For the questionnaire-based data collection researchers will verbally administer questionnaires directly to children. Parents can choose to self-complete or verbally complete questionnaires with the researcher. If the participant’s preferred language is not English, trained Community Researchers will administer the questionnaires and undertake other data collection using the relevant language. Researchers and families will be blind to their treatment allocation at the time of baseline measures. The feasibility of this data collection approach will be assessed to inform a future trial.

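### The October 2016 end of follow-up leaves no time for the programme itself, so families recruited after about mid-March 2016 cannot have a full 6-month visit by then

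*Protocol article*

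**What the plan says.** All references are to the protocol article.

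- **Calendar (Study status).** Enrolment into phase 2 started in September 2015 and is "due to finish in April 2016, and final follow-up measures will be undertaken by October 2016". This is the only statement of the follow-up calendar.
- **Visit schedule (Study design).** Data are collected "before programme attendance, after programme completion and 6 months after programme completion". Outcome data collection procedure repeats the anchor: "three time points: baseline, post-intervention and 6 months post-intervention".
- **Order of events (Participants).** Consent and baseline measurement take place at a home visit, and Study design puts baseline before attendance.
- **Programme length (Setting).** "First Steps is a group-based programme delivered as seven one-hour sessions over 6–7 weeks in community venues". Under Comparator arm, First Steps is what the comparator families receive. The length of the adapted programme is not given.
- **Target (Participants).** "We aim to recruit 80 children and their families in a 6-month period".

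The article gives no visit window for the last visit, no limit on the wait between recruitment and the first session, and no statement that late recruits will have shorter follow-up.

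**The concern.** October 2016 is six months after April 2016, the month in which recruitment closes. The last visit, however, is counted from the end of the programme, not from recruitment. The weeks spent in the programme, and any wait for it to start, do not appear in the calendar.

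If the October date is kept, late recruits either have no 6-month visit or are measured early under a 6-month label. Both matter to this study. Study aims and objectives lists feasibility of follow-up and data on attrition. Sample size gives recruitment and attrition rates as a reason for enrolling 80 families. Data analysis takes baseline–follow-up correlations from these data for the future sample size. A loss created by the calendar would be read as a property of the population, and mixed intervals would enter the correlations under a single label.

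**Working it through.** **Inputs.** Last recruit between 1 and 30 April 2016 (Study status, month only). Follow-up closes on 31 October 2016, the most generous reading of the stated month. Programme length is 6 or 7 weeks (Setting). The wait from recruitment to first session is not stated: it is taken as 0 weeks, the value most favourable to the plan, with 4 weeks as an assumed alternative.

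**Step 1: what reproduces October 2016.** 30 April 2016 + 6 months = 30 October 2016. The stated date is reached only if the six months run from recruitment.

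**Step 2: due date as defined.** Due date = recruitment + wait + programme length + 6 months.

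| Recruited | Weeks | Wait | Programme ends | Last visit due |
|---|---|---|---|---|
| 1 April | 6 | 0 | 13 May | 13 November 2016 |
| 1 April | 7 | 0 | 20 May | 20 November 2016 |
| 30 April | 6 | 0 | 11 June | 11 December 2016 |
| 30 April | 7 | 0 | 18 June | 18 December 2016 |
| 1 April | 6 | 4 weeks | 10 June | 10 December 2016 |
| 30 April | 7 | 4 weeks | 16 July | 16 January 2017 |

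With no wait, the overrun past 31 October is 13 to 48 days. On 31 October a 1 April recruit is 5.4–5.6 months past programme end, and a 30 April recruit 4.4–4.7 months.

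**Step 3: latest workable entry.** 31 October − 6 months = 30 April, the latest programme end. Subtracting 7 or 6 weeks gives entry by 12 or 19 March 2016 with no wait. With a 4-week wait it is 13 or 20 February.

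**Step 4: share affected.** Assume uniform entry from 1 September 2015 and 6–7 weeks in both arms. Share = (days from latest workable entry to end of recruitment) / (days of recruitment).

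- Recruitment ends 1 April, no wait: 13/213 to 20/213 = 6–9%, about 5–8 of 80.
- Recruitment ends 30 April, no wait: 42/242 to 49/242 = 17–20%, about 14–16 of 80.
- With a 4-week wait: 41/213 to 48/213 = 19–23%, and 70/242 to 77/242 = 29–32%.

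A start on 30 September instead of 1 September shortens both windows by 29 days. The no-wait shares then become 13/184 to 20/184 = 7–11% and 42/213 to 49/213 = 20–23%.

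**Step 5: dependence on the adapted programme's length.** A 30 April recruit must finish by 30 April, so any multi-week programme breaks the schedule. A 1 April recruit has 29 days, so only a programme of about 4 weeks or less, starting at once, would fit.

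**Step 6: illustration for attrition.** Suppose true 6-month attrition is 20% (an assumption) and unreachable families are counted as lost. Observed attrition is 0.20 + 0.80 × share. For shares of 6–9% this is 25–28%, and for 17–20% it is 34–36%.

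**The case against.** The dates come from a status paragraph in a journal article, given in whole months as a forecast. The operative definition of the visit is six months after completion. Nothing in the article makes October a hard stop or says that late families will be counted as lost. The forecast may simply slip and the visits take place when due. A visit window may also stand in the full protocol, which is not shown. This is fair, and it rules out saying what will happen to late families. It does not remove the inconsistency: the only published calendar does not fit the published visit schedule.

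The size is also open to challenge. Families join scheduled programmes, so entry may be uneven, and few may join after mid-March. The 6–7 weeks is documented only for First Steps, while 16 of the 24 programmes are the adapted one. Many affected families would be short by days or a few weeks: with an assumed 4-week window, the 30 April, no-wait case falls to 14–21 of 242 days, or 6–9%. All of this stands. The percentages are illustrations, and the effect on the correlations has not been quantified.

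A reader might also infer that the 6-month recruitment period in Participants is wrong, because September to April looks like seven or eight months. The article does not support this. Month-only dates allow anything from about 6 months (30 September to 1 April) to about 8, and Participants states an aim while Study status reports a later position.

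**Conclusion.** The point holds as an inconsistency between Study status on one side and Study design, Outcome data collection procedure and Setting on the other. For the comparator programme it needs no assumption beyond the article's dates: even a 1 April recruit who starts the same day and finishes in six weeks is due on 13 November 2016.

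The number affected is not determined by the article. It is about 6–20% of 80 with no wait, uniform entry from 1 September and 6–7 weeks in both arms, and more with any wait.

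Two stronger conclusions are tempting. One is that the study cannot deliver its 6-month visit; the calendar fails only for families entering after about mid-March. The other is that the main result is at risk; the primary outcome is completion taken from routine attendance data, and the Discussion rests the decision on a full trial primarily on completion and acceptability. What is exposed is the 6-month attrition estimate and the baseline–follow-up correlations. This is a minor to moderate correction.

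**What to change.** Reconcile the sections in one of two ways.

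1. Restate the final follow-up date as mid to late December 2016, or later if families wait for a programme (up to 16 January 2017 with a 4-week wait). The cost is about 2 to 7 more weeks of home visits with no wait, and correspondingly more with one.
2. Keep October 2016 and state that families whose programme ends after 30 April 2016 contribute baseline and post-programme data only. Treat them as administratively not due and exclude them from the 6-month retention denominator. This costs almost nothing beyond the 6-month data from those families.

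Under either option, record the actual interval from programme end to the last visit for every family and report its distribution beside the 6-month results, so that early visits can be seen. State the number of families not due separately from the number lost.

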## Abbreviations

BCW, Behaviour Change Wheel; BMI, body mass index; COM-B, capability, opportunity, motivation and behaviour; MRC, Medical Research Council; NCMP, National Child Measurement Programme; NHS, National Health Service; RCT, randomised controlled trial
